### Who will take informed consent? {26a}

F.R. will introduce the study and explain how to confirm the consent form via telephone. In addition, participants will be instructed to obtain information about the study from the “research information” and “about us” pages on Mehrpishgan website. Then, participants will complete and confirm the electronic consent form (Additional file 3) uploaded on Mehrpishgan website.

### Additional consent provisions for collection and use of participants’ data and biological specimens {26b}

This is not applicable. No biological specimens will be collected for research purposes, so additional consent from the participants will be not required.

### Interventions

#### Explanation for the choice of comparators {6b}

All recruited participants will be randomly allocated to one of the intervention or control groups after baseline measurement. The intervention will not be applied to the control group during the study. They will receive routine care during the trial. If the intervention would be effective, at the end of the study, the control group participants can use the contents of the website and take advantage of the support group in order to ethical consideration.

#### Intervention description {11a}

To form a web-based support group, we will provide a virtual, interactive, secure, and confidential information website in Persian language. To prepare the format and content of this website, we will assess the informational needs of the informal caregivers of elderly using a qualitative study. Then, we will review the existing printed and electronic materials and consult experts in the field. In addition, we will tap into similar websites, software, and applications.

We will use a content management system (WordPress). This website is compatible with a variety of devices, including smartphones, tablets, and PCs (responsive websites), so that people with different devices can use it. We prefer developing the website to mobile applications because it does not require software installation and will not take up a large space on electronic devices. In addition, websites are easily accessible using URLs and do not require specialized knowledge or particular computer skills to use. It also will be employable with public internet's standard speed. Furthermore, we will define different access levels based on the user type (intervention group, control group, and research team).

To achieve the study objectives, we will prepare a form to record the demographic characteristics of participants, an online questionnaire, an online chatroom, two asynchronous forums, an educational section, a form to send feedback questions and suggestions to the website manager (PI), and research guides and information pages to introduce research team members, describe the study objectives and the advantages and disadvantages of participation, and provide instructions for using the website.

After designing, Mehrpishegan website will be tested by a small group of users and then will be revised and fixed accordingly.

#### Intervention procedure

##### The Web-based support group

The intervention will be in the form of using Mehrpishegan website. The content of Mehrpishegan will include the skills needed by caregivers to care for the elderly and to manage their own mental health.

During the first 3 months, interactions between intervention group members in the online chatroom will take place through two theoretical and practical parts. In the theoretical part, information on the topic will be provided once a week at a certain time by the facilitator (a psychologist), and the intervention group will be encouraged to share information, problems, concerns, feelings, experiences, life stories, and possible solutions with their teammates and experts. The average duration of each session in an online discussion will be from 60 to 90 min. In the practical part, the facilitator will provide practical assignments to the members of the intervention group. Furthermore, members in the intervention group will be guided to use asynchronous forums to discuss questions and answers related to the elderly care and their own mental health issues. The participants can discuss their assignments in the chatroom and ask questions, as well as submit questions about uploaded educational content and receive answers accordingly. In the second 3 months, active members of the support group will lead online group discussions without the direct involvement of professional team members.

##### The control group

They will have access to the general interface of the website; but they cannot use facilities related to the intervention.

#### Criteria for discontinuing or modifying allocated interventions {11b}

Termination of care tasks (change of care status to non-primary caregiver, death or recovery of the elderly); the participant’s request; leaving the support group and not using the website; undergoing any kinds of medical treatments; emergence of an adverse issue during the study that seriously affects the individual’s mental health, such as divorce or death of close relatives; or any behavior that threatens or harms other participants will result in exclusion from the study or discontinuing the intervention.

To estimate the efficacy, all participants will be analyzed according to randomization assignment (ITT approach) as a full analysis set (FAS) population. In addition, per protocol (PP) approach will be done as well.

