#### Relevant concomitant care permitted or prohibited during the trial {11d}

Since the informal caregivers for elderly are not registered as caregivers in any health or social care system, they do not receive any special care services. As a result, participants will be able to obtain the same health and social services as the general public during the trial, but they will be excluded if they require mental health therapy.

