## Statistical methods

### Statistical methods for primary and secondary outcomes {20a}

All eligible participants in the study who will be randomly assigned to the groups will be considered the Full Analysis Set (FAS) that will make up the intent to treat analysis (ITT) population. The per-protocol population is a subset of the ITT population that has no violations of the study protocol (type of intervention and timing specified). Information on all quantitative data will be reported as mean (standard deviation) or median interquartile range (IQR), while qualitative data will be reported as frequency and percentage. We will compare the two groups to measure the effectiveness of the intervention and changes in the outcomes (depression, anxiety, and stress) over time using the repeated measures ANOVA test. The SPSS and STATA will be used for analysis of data.

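### Post-randomisation exclusion for needing mental health therapy, and an undefined choice between exclusion and stopping the intervention for non-use, conflict with the declared ITT analysis if exclusion ends follow-up

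*Protocol article*

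**What the plan says.** All references are to the protocol article.

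- **{11b}, criteria for discontinuing or modifying allocated interventions.** The listed events include the end of the caring role, the participant's request, "leaving the support group and not using the website; undergoing any kinds of medical treatments", and an adverse issue with a serious effect on mental health, with divorce or bereavement as examples. Together they "will result in exclusion from the study or discontinuing the intervention". No event is assigned to one consequence or the other.
- **{11b}, next paragraph.** "all participants will be analyzed according to randomization assignment (ITT approach) as a full analysis set (FAS) population"; a per-protocol analysis is added.
- **{11d}, concomitant care.** "participants will be able to obtain the same health and social services as the general public during the trial", followed by "but they will be excluded if they require mental health therapy".
- **{20a}.** "All eligible participants in the study who will be randomly assigned to the groups will be considered the Full Analysis Set (FAS"), and this set is the ITT population. The per-protocol set is the subset without protocol violations.
- **{20c}.** ITT again, with missing values filled in by simple linear regression.
- **The control group.** Controls see the general interface of the website but not the facilities of the intervention.
- **Outcomes {12}.** Depression, anxiety and stress on the DASS-21 are the three primary outcomes.

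**The concern.** An ITT analysis needs outcome data from randomised people whatever happens to their treatment. Here, events after randomisation can remove people from the study, and two of them are not neutral between arms or with respect to the outcome.

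- **Need for mental health therapy** is closely related to all three primary outcomes. Removing these people takes out poor outcomes in both arms, and at different rates if the intervention has an effect.
- **Leaving the support group and not using the website** cannot happen in the control arm, which has no support group to leave. If this leads to exclusion, only the intervention arm is filtered.

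An analysis plan cannot repair this later, because T1 and T2 scores that were never requested cannot be recovered. The choice between the two consequences in {11b} is also left to people who know the allocation: under {17a} only the data analyst is blinded.

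There is a separate internal conflict. Read literally, {11b} makes medical treatment of any kind a trigger, while {11d} lets participants use ordinary health services during the trial.

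**Working it through.** **1. The plan's own figures.** The sample size section {14} gives an effect size of 0.50, alpha 5%, power 80%, 63 per arm, 20% drop-out and 80 per arm. With two-sided alpha, n = 2(1.960 + 0.842)² / 0.50² = 62.8, so 63 per arm. Then 63/0.80 = 78.75, so 79; the t-test version gives 64, and 64/0.80 = 80. The stated size reproduces and is not in dispute.

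**2. The statements side by side.**

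| Event after randomisation | Consequence stated | Arm | Link to primary outcomes |
|---|---|---|---|
| Needs mental health therapy ({11d}) | Exclusion, no alternative | Both | Direct |
| Leaves group and does not use website ({11b}) | Exclusion or stopping the intervention, not specified | Intervention only | Plausible, unknown |
| Any medical treatment ({11b}) | As above, and in conflict with {11d} | Both | Unknown |
| Serious life event ({11b}) | As above | Both | Indirect; the examples are external events |

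The ITT statements in {11b}, {20a} and {20c} are compatible with the third column only if these people are still assessed at T1 and T2. The article does not say whether they are.

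**3. Illustration: non-users deleted from one arm, no true effect.** Assumptions: a share f = 20% of the intervention arm is removed (this borrows the plan's overall drop-out allowance; the article gives no rate for this event), and a latent tendency to leave has correlation r = 0.3 to 0.5 with a worse outcome. With the cut at z = 0.842 and normal density φ(z) = 0.280, the retained mean shifts by r × φ(z)/(1 − f) = r × 0.280/0.80 = 0.350r.

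- r = 0.3: 0.350 × 0.3 = 0.105 SD
- r = 0.5: 0.350 × 0.5 = 0.175 SD

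This leaves 80 controls and 64 in the intervention arm, so SE = √(1/80 + 1/64) = 0.168. The two-sided 5% test then rejects a true null with probability Φ(−1.96 + 0.105/0.168) + Φ(−1.96 − 0.105/0.168) ≈ 10% for r = 0.3, and by the same formula about 18% for r = 0.5.

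**4. A second model as a check.** If the excluded share f scores m SD worse than those retained, the bias is f × m. With f = 20%:

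| m (assumed) | Spurious benefit | Rejection rate |
|---|---|---|
| 0.25 SD | 0.05 SD | 6.0% |
| 0.50 SD | 0.10 SD | 9.2% |
| 1.00 SD | 0.20 SD | 22.2% |

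**5. What the declared imputation changes.** Steps 3 and 4 delete people outright, which is not the declared analysis. If the missing scores are predicted from retained participants of the same arm, the bias is again f × m, but m is now the gap that remains after allowing for the predictors. Imputation removes the part that the predictors explain and none of the rest. The remainder is not identifiable from the article. Single imputation also understates the standard error.

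**6. The direction is not fixed.** Suppose instead that a common threshold removes the worst 5%, 10% or 15% of controls (assumed), is applied to both arms, and the true effect is 0.50 SD. Truncated-normal means give a difference of 0.43, 0.39 or 0.36 in units of the original SD. Divided by the SD of those retained, it is 0.47, 0.44 or 0.42. This selection dilutes the effect, where step 3 inflates it.

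**The case against.** The strongest reply is that {11b} allows stopping the intervention as an alternative, stands under a heading about discontinuing or modifying the intervention, and is followed at once by the ITT statement. {20a} puts protocol violators outside the per-protocol set only. For non-use there is thus a coherent reading: stop the intervention, leave the per-protocol set, stay in the FAS. Nothing says in so many words that follow-up stops, T1 and T2 are scheduled in both groups, and reminders are planned at each stage. This stands as far as non-use goes: the text is ambiguous there, not plainly contradictory. It does not cover {11d}, where exclusion for therapy has no alternative.

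Three stronger readings are tempting and are not supported.

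- **That non-users will be removed from the intervention arm.** {11b} permits this but does not require it.
- **That the serious adverse issue is itself a bad result on the primary outcomes.** The examples are external life events that can befall either arm. Only the therapy rule clearly selects on the outcome.
- **That harms are hidden.** Section {22} commits to collecting all adverse events, related or not, with causality assessment and individual reporting.

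It is also fair to say that the illustrated bias describes deletion under assumed rates, not the declared imputed ITT. It must not be read as an estimate for this trial.

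**Conclusion.** The concern holds in a conditional form. Section {11d} excludes randomised participants who come to need mental health therapy, and {11b} leaves open whether the other events, including one that can occur only in the intervention arm, mean exclusion or merely stopping the intervention. If exclusion ends follow-up, this conflicts with the ITT/FAS analysis of everyone randomised: poor outcomes are lost selectively, and those people count only through a single regression imputation that treats them like retained participants with the same predictors.

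Neither the size nor the direction of the bias can be derived from the article. A spurious benefit of 0.105 to 0.175 SD is about one fifth to one third of the design effect (0.105/0.50 = 21%; 0.175/0.50 = 35%). It rests on an assumed 20% deletion in one arm and an assumed correlation of 0.3 to 0.5. It shows that the wording can matter, not how much it will. The point should be settled before follow-up assessments begin, because missed scores cannot be collected afterwards.

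**What to change.** In {11b} and {11d}, separate two things that are now merged: stopping the intervention and leaving the study. Whatever clinical rules the team keeps for stopping or continuing website access, add that:

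1. the T1 and T2 DASS-21 are requested from every randomised participant unless consent for follow-up is withdrawn;
2. all of them stay in the FAS with their observed data, so that imputation is needed only for scores that could not be obtained;
3. the listed events serve only to define the per-protocol set;
4. the date and reason of each event are recorded and reported by arm.

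The team must also reconcile the medical-treatment trigger in {11b} with the access to ordinary health services in {11d}. This review takes no position on which rule should stand.

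The cost is a wording amendment with the usual notification. The questionnaires are already online and SMS reminders are planned at each stage, so the extra follow-up costs little. The sample size does not change.

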#### Strategies to improve adherence to interventions {11c}

Logging in to the website will be through a personal username and password, and approval of the administrator (FR) in order to maintain confidentiality and protect adherence. Participants in the interventional group will learn how to properly use different parts of the website such as support group, forums, and educational content. In addition, participants will be reminded to join the group and forums at the appropriate times via short message service (SMS)/notifications. Participants will be encouraged to take part in discussions and read the summary file prepared by the facilitator. Also, the researchers will participate in the support group and forums in order to increase their common sense and oversight. Participants will be able to send their comments and suggestions through the website and contact the researcher/facilitator in case of any problems.

#### Relevant concomitant care permitted or prohibited during the trial {11d}

Since the informal caregivers for elderly are not registered as caregivers in any health or social care system, they do not receive any special care services. As a result, participants will be able to obtain the same health and social services as the general public during the trial, but they will be excluded if they require mental health therapy.

#### Provisions for post-trial care {30}

The website will be maintained to answer the questions of the participants about elderly care post-trial. Participants can use a free consultation with a psychologist, attend a psychology workshop, or receive free related books after the trial. Although the nature of the study is educational and supportive and does not appear to be harmful, in the event of reporting adverse effects, researchers will be responsible for following up until the problem is resolved or paid for.

### Outcomes {12}

This study has three primary outcome variables (depression, anxiety, and stress) that are going to be measured by the DASS-21 scale three times during the study: before (T0), by the end of the first 3 months of the intervention (T1), and by the end of the second 3 months (T2) after the intervention. The effect of the web-based support group on depression, anxiety, and stress in the intervention and control groups will be assessed and compared before and after the intervention. The difference in the mean scores of the outcomes will be assessed.

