## Objectives {7}

This is the protocol for our study, which aims to assess the effect of Mehrpishegan web-based support groups on depression, anxiety, and stress in elderly informal primary caregivers. The hypothesis of this study is that there is a difference in the status of depression, anxiety, and stress among the participant caregivers before and after implementing the intervention.

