### Sample size {14}

The study population consists of informal primary caregivers of the elderly in the South Tehran, who have the willingness to participate. The sample size has been calculated using PASS 15.0.5 software. Based on literature [18] and using Cohen’s formula (expecting the average effect size) with a coefficient = 0.5 φ [19], for both of the intervention and control groups (63 people), taking into account the power of 80. The effect size is 0.50 and the significance level (alpha) will be 5%, the probability of drop-out and withdrawal of the study is 20%, equivalent to 80 people in each group, and the total will be 160 people.

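### Three primary outcomes share one unadjusted 5% level with no success rule or primary time point, while the sample size covers a single unspecified comparison; the stated 5% and 80% are not established for the trial's conclusion

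*Protocol article*

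**What the plan says.** The Outcomes section {12} states: "This study has three primary outcome variables (depression, anxiety, and stress"). The follow-up assessments come "by the end of the first 3 months of the intervention (T1), and by the end of the second 3 months (T2"). Neither time is called primary and no outcome is placed ahead of the others.

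The Objectives section {7} puts all three into one hypothesis, that "there is a difference in the status of depression, anxiety, and stress among the participant caregivers before and after implementing the intervention". It does not say whether a difference on one scale is enough or whether all three must differ.

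The Sample size section {14} makes one calculation, "for both of the intervention and control groups (63 people"), "taking into account the power of 80". It continues: "The effect size is 0.50 and the significance level (alpha) will be 5" per cent. With 20% dropout this becomes 80 per group and 160 in total. The 0.50 is not tied to a named scale or a named time.

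The Statistical methods section {20a} compares the groups on "changes in the outcomes (depression, anxiety, and stress) over time using the repeated measures ANOVA test". It gives no order of testing, no division of alpha and no success rule.

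**The concern.** A 5% level and 80% power describe one test. This trial has three co-listed primary outcomes, and its conclusion will be drawn from all of them. What the error rate and power are for that conclusion depends on a rule that the protocol does not give:

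- If a significant result on any one scale supports a claim that the support group works, there are three chances of a false positive and the 5% no longer bounds the error of that claim.
- If all three scales must be significant, the error is controlled but 80% power for each scale is not 80% for the set.
- If alpha is divided across the scales, the error is controlled but a sample sized at an undivided 5% gives less than 80% for any given scale.

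The missing primary time point adds a second gap. Under Intervention procedure, months 1 to 3 are led by a psychologist and months 4 to 6 by active members without direct professional involvement. T1 and T2 therefore answer different questions, and the effect size of 0.50 could refer to either.

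**Working it through.** **Inputs from the protocol article.** Three primary outcomes, with T1 and T2 after baseline (Outcomes). Alpha 5%, power 80%, effect size d = 0.50, 63 per group, 20% dropout, 80 per group (Sample size). Allocation 1:1 (Trial design). Repeated measures ANOVA of the three outcomes (Statistical methods).

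**Assumptions.** Two-sided testing: sidedness is not stated, but one-sided testing would give 50 per group, not 63. The correlation between scales is not given, so a range of 0 to 0.8 is used. Where power on several scales is computed, d = 0.5 is taken to hold on all of them.

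**1. The plan's own figure.** n per group = 2(z₀.₉₇₅ + z₀.₈₀)²/d² = 2(1.960 + 0.842)²/0.25 = 62.8, so 63. This matches. With the t distribution, power is 79.5% at 63 and 80.1% at 64 per group. Dropout: 63/0.8 = 78.75 (79) and 64/0.8 = 80. The 80 per group thus leaves 80 × 0.8 = 64 completers. The calculation is sound for one comparison.

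**2. Any one scale counts as success, each tested at 5%.** If the scales are independent, familywise error = 1 − 0.95³ = 14.3%. For correlated scales, simulation of three multivariate normal test statistics gives:

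| Correlation | Familywise error | Power, at least one scale (63 per group) |
|---|---|---|
| 0 | 14.3% | 99% |
| 0.3 | 13.6% | 97% |
| 0.5 | 12.5% | 95% |
| 0.7 | 10.9% | 92% |
| 0.8 | 9.8% | 90% |

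The error is about two to three times the stated 5%. Power is above 80%.

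**3. All three scales required, each tested at 5%.** If independent, power = 0.801³ = 51% to 52% at 63 per group and 0.807³ = 53% at 64. With correlation:

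| Correlation | Power at 63 | Power at 64 |
|---|---|---|
| 0 | 52% | 53% |
| 0.5 | 61% | 62% |
| 0.7 | 66% | 67% |
| 0.8 | 69% | 70% |

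The chance of three false positives when no scale has an effect is 1.4% or less over this range. Error is controlled and power falls short.

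**4. Alpha controlled across the three scales, 64 completers per group.**

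- *One given scale at 0.05/3 = 0.0167.* The critical value is 2.394 and the expected test statistic is 0.5 × √(64/2) = 2.828. Power = P(Z > 2.394 − 2.828) = 67% by the normal approximation and 66% with the t distribution. This is the worst case for one pre-specified scale.
- *Holm's procedure.* The first step compares the smallest of the three p-values with 0.0167, so its power is the chance of at least one rejection. Simulation gives 96%, 88%, 83% and 80% at correlations 0, 0.5, 0.7 and 0.8. Average power per scale is 76%, 74%, 74% and 73%.
- *Fixed order.* The first scale is tested at the full 5% and keeps 80%. Later scales are reached only if the earlier ones succeed.

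**The case against.** The strongest reply is that multiplicity procedures are commonly left to the statistical analysis plan, which is not shown, and that a journal article condenses. That is fair as to the adjustment procedure itself, whose absence alone would not be a finding. It does not reach the sample size. The number of primary outcomes, the 5% level and the 63 per group are all fixed in this document, and the 63 follows only from an undivided 5% on one comparison. A later plan could add an adjustment, but the 80% would then no longer describe a given scale.

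A second reply is that each scale might be reported as its own conclusion, so that 5% and 80% hold scale by scale. The protocol does not say this, and the Objectives section puts the three scales in one hypothesis.

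Three stronger readings are tempting but not supported:

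- *Six tests.* A reader might count three scales at two follow-up times and quote a still higher error rate. The Statistical methods section plans repeated measures ANOVA over time, which takes both follow-ups into one model per outcome. Separate 5% tests at T1 and T2 are not stated. The supported count is three.
- *Both figures fail.* A reader might infer that the 5% and the 80% are both wrong whatever the rule. They are not: the any-one rule breaks the 5% but has 90% to 99% power, and the all-three rule keeps the 5% but loses power.
- *Access for controls.* A reader might infer that an inflated error rate decides whether controls are offered the website, because the comparator section makes this depend on effectiveness. The Recruitment section offers access after T2 without that condition, so this consequence cannot be relied on.

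**Conclusion.** The point holds in this form: three primary outcomes, one unadjusted 5% level, no success rule, no primary time point, and a sample size that covers one unspecified comparison. The stated 5% and 80% are correct for that comparison and not established for the trial's conclusion. The familywise error is about 10% to 14% if any one scale suffices. Power is about 52% to 70% at 63 to 64 per group if all three are required. These ranges rest on assumed correlations of 0 to 0.8 between scales and two-sided tests, and the power figures also on d = 0.5 for every scale. The lack of a primary time point leaves the target of the 0.50 undefined, but does not by itself multiply the number of tests.

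**What to change.** - **Outcomes {12}:** name one primary time point and state the success rule (any scale, or all three). The choice of time is the sponsor's, since T1 closes the facilitator-led phase and T2 the member-led phase; the other time becomes secondary.
- **Statistical methods {20a}:** test the group effect on the three DASS-21 scales at that time with Holm's procedure at an overall two-sided 5%, or in a pre-specified fixed order with each scale at 5%.
- **Sample size {14}:** say which comparison the 0.50 refers to and restate power under the chosen rule. For Holm with 64 completers per group and d = 0.5 on all three scales, this is about 80% to 96% for at least one scale and 73% to 76% on average per scale, depending on the correlation. The 66% figure should be given only as the worst-case Bonferroni power for one given scale, not as the power of Holm's first step. A fixed order keeps 80% for the first scale only.

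The cost is a few sentences and a less favourable stated power per scale. No extra participants are needed. The change should be made before any unblinded analysis. If the sponsor instead wanted 80% power for each given scale at 0.0167, the normal approximation gives 84 per group, or 84/0.8 = 105 after dropout and 210 in total, which is 50 more than planned.
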